# ７．Target number of the included patients and rationale for setting

　　【Target number of the included patients 】100

【Rationale for the target number】

We calculated the probability of verifying a significant difference in the primary endpoint between the groups (statistical power) in this number of cases. When the endotracheal intubation rate in the non-treated group was set at 22% and that in the treated group at 10%, and α = 0.1 (one-sided), the statistical power was 0.6406.

The rate of endotracheal intubation in the non-treated group is based on the National Institute of Infectious Diseases (Japan), and according to information published on the Web, of 287 cases of COVID-19 infection as of March 9, 2020, information on invasive ventilation was available for 133 cases. Of these, 29 (22%) were reported to have undergone endotracheal intubation.（<https://bit.ly/3eiiMhg>）。

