For the primary endpoint of endotracheal intubation rate, if the null hypothesis "the rate of endotracheal intubation in the non-treated group is equal to the rate of endotracheal intubation in the treated group" is rejected, it was judged to be effective. If not, it is considered invalid from a clinical medical standpoint. The significance level for the entire study is set at 10% on one side. No adjustment for multiplicity will be made.

【Efficacy analysis 】

The analysis of efficacy is based on the treatment assigned to the patients by the minimization method according to the intention-to-treat (ITT) principle. An ITT analysis is defined as a method of analysis based on the assignment of a treatment group to a treatment or non-treatment group that is determined prior to the initiation of the intervention, rather than on the actual intervention performed. For example, patients who are assigned to the treatment group but never receive treatment for some reason are treated as the treatment group.

Analysis of the primary endpoint (endotracheal intubation rate)

1. Method of main analysis

Based on the observed endotracheal intubation rate, a binomial test will be performed for the null hypothesis that "the rate of endotracheal intubation in the non-treated group is equal to the rate of endotracheal intubation in the treated group. The competing hypothesis will be "the tracheal intubation rate of the treated group is less than that of the non-treated group". If the null hypothesis is rejected, the test is considered valid; if not, the test is considered clinically invalid. The risk ratio is calculated by dividing the risk of tracheal intubation in the treated group by the risk of tracheal intubation in the non-treated group. The exact 90% confidence interval based on the binomial distribution will be used to estimate the interval of the risk ratio.

1. Subgroup analysis will be conducted based on the factors described below.

＜Factors for which subgroup analysis is planned＞

Under 70 years old / Over 70 years old ・ Male / Female ・ Smoking history/No smoking history

Analysis of secondary endpoints (mortality)

The analysis will be performed in the same way as for the primary endpoint.

【Safety analysis】

Calculate the number and percentage of patients in the CTCAE version 5.0 Grade 1 to Grade 5 groups in the treated and non-treated groups, respectively.

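### The binomial test named for the primary endpoint is not the test behind the stated power of 0.6406; one two-sample test should be named and its power stated

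*Protocol*

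**What the plan says.** **Section 7** (target number). The total is 100. The intubation rate is set at 22% without and 10% with teprenone, and the power statement reads "α = 0.1 (one-sided), the statistical power was 0.6406". No test is named and no allocation ratio is given as a number.

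**Section 8** (main analysis). The hypotheses are those of a two-group comparison: equal rates under the null, and under the alternative "the tracheal intubation rate of the treated group is less than that of the non-treated group". The level agrees with section 7: "The significance level for the entire study is set at 10% on one side". The test is introduced with "Based on the observed endotracheal intubation rate, a binomial test will be performed for the null hypothesis that" the two rates are equal. For the effect measure, "The exact 90% confidence interval based on the binomial distribution will be used to estimate the interval of the risk ratio". No chi-square, z, Fisher or unconditional exact test is named anywhere. Rejection of this null is the only criterion for calling the treatment effective, and mortality is to be analysed in the same way.

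**The concern.** In usual language a binomial test compares one observed count with a known rate. Here both arms are observed and section 8 gives no reference rate, so the named test does not identify a procedure for the stated hypotheses. An analyst could:

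- treat the observed control rate as known, which ignores its sampling error;
- test whether the events split evenly between the arms;
- take the word exact as the guide and run Fisher's test; or
- run the large-sample comparison of two proportions.

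These differ in type I error and power, and on some data they give opposite verdicts. The test carries the whole effective / not effective decision in an open-label trial, and section 8 leaves changes to the analysis plan to the investigators. The test should therefore be fixed without room for choice.

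**Working it through.** **Inputs.** N = 100, rates 0.22 and 0.10, one-sided α = 0.10 (section 7; α repeated in section 8). Assumed: 50 per arm, since no ratio is stated, and all 100 patients analysed.

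**Step 1: reproduce the stated power.** Two-sample z test, pooled variance under the null, no continuity correction:

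power = Φ[(p₁ − p₂ − z·SE₀) / SE₁]

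- pooled rate = (0.22 + 0.10)/2 = 0.16
- SE₀ = √(2 × 0.16 × 0.84 / 50) = 0.07332
- SE₁ = √(0.22 × 0.78/50 + 0.10 × 0.90/50) = 0.07233
- z = 1.28155 for one-sided 0.10
- power = Φ[(0.12 − 0.09396)/0.07233] = Φ(0.3599) = 0.64055

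This rounds to the stated 0.6406. Other one-sided formulas miss it: unpooled z 0.6471, arcsine 0.6491, log risk ratio 0.6150, log odds ratio 0.6251, pooled z with continuity correction 0.5332.

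**Step 2: power and size of the candidate tests.** All 51 × 51 outcomes are enumerated with binomial probabilities, rejecting when the one-sided p-value is at most 0.10. Power is at 22% against 10%. Maximum size is over common rates up to 50%.

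| Test | Power | Type I error at 22% | Maximum size |
|---|---|---|---|
| One-sample binomial, observed control rate taken as fixed | 0.708 | 0.140 | 0.166 |
| Binomial on the split of events (½ each) | 0.492 | 0.046 | 0.048 |
| Fisher, one-sided | 0.553 | 0.065 | 0.069 |
| Fisher mid-p | 0.640 | 0.097 | 0.097 |
| Boschloo | 0.619 | 0.093 | 0.097 |
| Pooled z | 0.648 | 0.099 | 0.12 |

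The one-sample reading exceeds the stated 10% level. The event-split and Fisher readings keep the level but fall well short of 0.6406. Pooled z has size 0.100 at a common rate of 16% and 0.105 at 10%; its maximum of about 0.12 occurs at a low common rate, near 3.5%.

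**Step 3: can the choice change the verdict?** One-sided p-values, control events against treated events:

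| Test | 11/50 vs 5/50 | 11/50 vs 6/50 |
|---|---|---|
| One-sample, observed control rate fixed | 0.023 | 0.056 |
| Pooled z | 0.051 | 0.092 |
| Fisher mid-p | 0.056 | 0.099 |
| Boschloo | 0.067 | 0.106 |
| Fisher | 0.086 | 0.143 |
| Event split | 0.105 | 0.166 |

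Examples for 11 vs 6: one-sample is P(X ≤ 6) for Bin(50, 0.22) = 0.056. Event split is P(X ≤ 6) for Bin(17, ½) = 0.166. Pooled z is 0.10/√(2 × 0.17 × 0.83/50) = 1.331, so p = 0.092.

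At exactly the planned rates (11 vs 5) only the event-split test fails. With one more treated event, three tests succeed and three fail.

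**The case against.** The strongest reply is that the hypotheses are correctly written for two groups and no reference rate appears, so the binomial test is probably loose or translated wording for a comparison of two binomial proportions. The match of 0.6406 to four decimals supports the pooled z test as what the planners had in mind. On that reading the stated power stands, and the level is met at the planned rates (0.099 at 22%, 0.100 at 16%). The one-sample reading also needs a plug-in step that the text never describes, and the event-split test presumes equal arms, which minimization does not guarantee.

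Much of this holds. It limits the point to a wrong or ambiguous test name that does not match the power calculation. It does not remove the point, because the same paragraph asks for an exact interval from the binomial distribution, which points away from the large-sample test behind 0.6406. A reader cannot settle from the protocol which test decides the trial.

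Three stronger conclusions might be drawn, and none is supported:

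- **A binomial test can never compare two arms.** The event-split version does, with power 0.49.
- **No test of exact type keeps both level and power.** Fisher mid-p, which is quasi-exact, has power 0.640 and maximum size 0.097.
- **The stated power or level is wrong.** That follows only under the literal readings.

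**Conclusion.** The concern holds as a mismatch between the named test and the power statement. Depending on the reading, following section 8 as written gives power 0.71 with type I error 0.14 (up to 0.17), power 0.49, or power 0.55, against a stated 0.6406 at 10%. The choice can reverse the verdict, as 11/50 against 6/50 shows. The 0.6406 itself is reproduced, and if the pooled z test was meant the correction is to the test name, with the caveat that its size reaches about 0.12 at low common rates. That caveat could matter for mortality if deaths are few, because the same method is carried over. All figures assume 50 per arm and no dropout. Severity: should-fix.

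**What to change.** In section 8, replace the binomial test by one named two-sample test at one-sided 0.10, and name a two-sample interval method for the risk ratio. In section 7, state the 1:1 allocation and the power of that test:

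- **Pooled z (chi-square):** 0.64, so the present figure stands; accept size up to about 0.12 at low rates.
- **Fisher mid-p:** about 0.64, maximum size 0.097.
- **Boschloo:** about 0.62, maximum size 0.097. A matching risk-ratio interval does not follow simply, because the test orders outcomes by Fisher's p-value, which is tied to the odds ratio. The interval method must be named separately.
- **Fisher:** 0.55.

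The smallest change is to name the pooled z test. The choice should be made before any comparison of outcomes by arm. The cost is a few sentences in two sections and the review committee approval that section 14 requires for protocol changes. Sample size and data collection are unaffected. The stated power falls only if Boschloo or Fisher is chosen.

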# ９．Research period

　December 31, 2024 from the date of publication of the jRCT after approval by the accredited clinical research review committee. 　（Registration deadline: December 31, 2023）

# １０．Inclusion and exclusion criteria

（１）Inclusion criteria

　　All of the following criteria must be met.

1. Age 20 years or older on the date of obtaining consent
2. Diagnosis of COVID-19 is confirmed by PCR or antigen test.
3. Fever of 37.5 degrees or higher
4. Written consent to participate in this study.

（２）Exclusion criteria

　　Patient that fall under any of the following criteria is excluded from this study.

- - 1. Patients with a history of teprenone medication within 2 weeks prior to the planned start of treatment
    2. Patients who require ventilator management or extracorporeal membrane artificial lung (ECMO) management
    3. Patients with apparently active infectious diseases other than SARS-CoV-2 (Nontuberculous mycobacterial infection that does not require treatment or has not progressed for more than one month even with treatment can be enrolled.
    4. Pregnant or lactating patients
    5. Patients whose identity information is not available

# １１．Background and scientific rationale for the study (rationale and validity of the study)

Background

As described previously (3. Background, objective and significance of the study), we are in the midst of a global pandemic of COVID-19, and the development of treatment to prevent severe disease as well as the development of antiviral drugs is an urgent issue. Treatment for prevention of severe disease is a therapeutic strategy that should be used in combination with antiviral therapy to be developed in the future. Therefore, a treatment method with as few adverse events as possible and easy access to therapeutic agents would be ideal.

Rationale and validity of the study

The purpose of this study was to investigate the effect of teprenone on the prevention of aggravation of COVID-19. We believe that a randomized controlled trial with and without teprenone is a reasonable study design to achieve the purpose of this study.

Fever is one of the major symptoms of COVID-19, and the time to fever resolution is a reasonable primary endpoint.

A network of five major public hospitals, including Okayama University Hospital (Okayama Medical Cooperation Promotion Council), a clinical trial network in the Chugoku-Shikoku region, and designated medical institutions for Class II infectious diseases in the Kanto and Kinki regions are planned as the research system, and an appropriate system is in place to register the planned 100 cases.

Although it is difficult to accurately predict the number of COVID-19 cases, we believe that the planned number of cases can be enrolled within the study period, because more than 2,600 cases have been observed in Japan as of April 3, 2020, and the number of cases is rapidly increasing.

# １２．Procedures for obtaining informed consent

　The principal investigator or sub-investigator will provide the research subject with an explanation document that has been approved by an accredited clinical research review committee, and will provide sufficient written and oral explanations. Normally, free consent will be obtained in writing, but in this study, from the viewpoint of infection prevention, if free verbal consent is obtained from the research subject, a consent form will be prepared by the physician and a nurse or other witness who is not involved in the study. If the research subject recovers from COVID-19 infection, re-consent will be obtained whenever possible when all isolation restrictions, including home isolation, are no longer necessary.

When information on efficacy and safety, etc., that may affect the consent of research subjects is obtained, or when changes are made to the implementation plan, etc., that may affect the consent of research subjects, information will be promptly provided to the research subjects, and the will of the research subjects as to whether or not to participate in the research, etc., will be confirmed in advance. At the same time, the explanatory documents and consent documents, etc. will be revised with the approval of the Accredited Clinical Research Review Committee, and the research subject's consent will be obtained again. At that time, if the research subject has not yet recovered from COVID-19 infection, the method of obtaining consent shall be the same as the method of obtaining consent the first time.

The consent document includes the following information

①The name of the specific clinical research to be conducted, the fact that approval has been obtained from the administrator of the medical institution for the conduct of the specific clinical research, and the fact that an implementation plan has been submitted to the Minister of Health, Labour and Welfare.

②The name of the medical institution where the research is to be conducted and the name and title of the principal investigator (in the case where the specified clinical research is to be conducted as a multi-center collaborative research, including the name and title of the principal investigator, the name of the other medical institution, and the name and title of the principal investigator of said medical institution).

③Reason for being selected as a subject of the study

④Anticipated benefits and disadvantages of the study

⑤Refusal to participate in the study is possible

⑥Matters concerning withdrawal of consent

⑦A statement that no disadvantage will be caused by refusal to participate in the study or withdrawal of consent.

⑧How to disclose information about research

⑨The fact that the research subject or his/her representative may obtain or inspect the research protocol and other materials related to the conduct of the specified clinical research upon request, and the method of obtaining or inspecting such materials.

⑩Matters concerning the protection of personal information of research subjects

⑪Methods of storage and disposal of samples, etc.

⑫Involvement of the pharmaceutical product manufacturer or seller in the study and the details thereof

⑬Contact for responding to complaints and inquiries

⑭Matters related to expenses

⑮Availability of other treatments and comparison with anticipated benefits and disadvantages of other treatment

⑯Matters concerning compensation for health damage and provision of medical care

⑰Matters to be reviewed by the Accredited Clinical Research Review Committee, which provides review and opinion services for research and other matters related to the Authorized Clinical Research Review Committee for the study

⑱Other matters necessary for the implementation of the study

# １３．Handling of personal information, etc. (including methods of anonymization)

All researchers involved in this research will conduct it in compliance with the Declaration of Helsinki and the Clinical Research Act. When handling information related to the implementation of the research, a unique research ID will be assigned to each research subject, and a list of correspondences between names and research IDs will be created. When sending information to the research secretariat, etc., an identification number will be used, and sufficient care will be taken to ensure that the research subject's name, date of birth, and other information is not leaked outside the hospital. Names will be deleted from the original data and used for research. Throughout the research period, the corresponding table files will be password protected and stored securely to prevent leakage. The person responsible for the management of materials, samples, and personal information at each institution will follow the procedures of each institution.

When publishing the results of research, do not include information that can immediately identify the research subjects, such as names and dates of birth. In addition, do not use the information on research subjects obtained in the research for purposes other than those of the research.

# １４．Burdens, anticipated risks, and benefits to research subjects, a comprehensive assessment of these, and measures to minimize such burdens and risks

（１）Anticipated benefit

　　There is no direct benefit from participating in this study. Research results may contribute to future medical advances.

（２）Anticipated disadvantages (side effects)

　Study subjects will be required to take oral teprenone for 10 days. There is a possibility that the study treatment may cause illness. According to the package insert of the investigated drug, the most common adverse reactions are increased AST/ALT (less than 0.1-5%), and other adverse reactions such as constipation, diarrhea, nausea, dry mouth, abdominal pain, abdominal distention, headache, rash, pruritus, increased total cholesterol, and

Eyelid redness and burning sensation are all considered to have a probability of less than 0.1%.

（３）Response to research subjects in the event of an adverse event

When an adverse event is recognized, the principal investigator or sub-investigator should immediately take appropriate measures and record the event in the medical record and case report form. If the administration of the study drug is discontinued, or if treatment for the adverse event becomes necessary, the research subject will be informed.

（４）Changes to the research protocol, etc.

Information necessary for the safe conduct of clinical research will be collected and reviewed. If new safety information is obtained, the research protocol and consent explanatory document will be revised as necessary. Any changes or revisions to the research protocol or consent explanatory document will require prior approval from the Accreditation Clinical Research Review Committee. When changes are made to the research plan, the following notification form shall be submitted to the Minister of Health, Labor and Welfare.

①Notification of changes to the protocol (Ministerial Order Form No. 2)

②Protocol after change

When the following minor changes are made to the protocol, the changes shall be notified to the accredited clinical research review committee within 10 days of the change. In addition, a notification form (Ministerial Order Form No. 3) shall be submitted to the Minister of Health, Labor and Welfare.

①A change in the name of the person engaged in the research that does not involve a change in the person engaged in the study.

②Changes due to a change in the name of the region or a change in the lot number

（５）Discontinuation criteria for individual research subjects

【What to do when the study is discontinued】

When the principal investigator or sub-investigator judges that it is impossible to continue the research on an individual research subject for any of the reasons listed below, the research on that research subject will be discontinued. In such cases, the reason for discontinuation will be explained to the research subjects as necessary. Regarding the treatment of the research subjects after the discontinuation, we will respond in good faith so as not to disadvantage the research subjects.

【Discontinuance criteria】

①If the research subject declines to participate in the research or withdraws his/her consent

②If the continuation of this study is judged to be difficult due to the progression of COVID-19 or its complications.

③Intolerable adverse events

④In case the study itself is discontinued

⑤If, for any other reason, the principal investigator or sub-investigator decides that it is appropriate to discontinue the research（In this case, record the reason for the discontinuation.）

【What to do when study treatment is discontinued】

If the principal investigator or sub-investigator determines that it is not possible to continue the study treatment for an individual research subject for any of the reasons listed above, the investigator or sub-investigator will discontinue the study treatment for that research subject. In this case, the reason for discontinuation will be explained to the research subject as necessary. In addition, the treatment of the research subject after discontinuation will be handled in good faith so as not to disadvantage the research subject.

Of the patients who discontinued study treatment, those who received the study drug will continue to be observed for safety evaluation.

# １５．Method of storage and destruction of information including storage period

The principal investigator shall prepare a record of the following items

①Items that identify the subjects of this research

②Matters related to medical treatment and examination of the subjects of this research

③Matters related to participation in this study

④Other matters necessary to carry out this research

The samples and information collected in this study will be stored in a lockable place (at a location designated by the implementing medical institution) until five years after the end of the study, after which they will be disposed of with due care for personal information. Information that can immediately identify individuals, such as names, addresses, and dates of birth, should be deleted from the stored information.

The principal investigator shall keep the essential documents related to the implementation of the research, etc. (research protocol, implementation plan, documents related to the explanation to the subjects of this research and their consent, summary report and other documents prepared by the principal investigator pursuant to the provisions of the ministerial ordinance, or copies thereof, documents related to the review opinion work received from the authorized clinical research review committee, documents related to monitoring, list of identification codes for research subjects, consent forms, copies of case reports, etc., and other documents or records necessary to ensure the reliability of the data, etc.) for five years after the completion of the research. (documents related to monitoring, lists of identification codes for research subjects, consent forms, copies of case report forms, and other documents or records necessary to ensure the reliability of data, etc.) shall be stored in a lockable place (at a location designated by each medical institution) until five years after the end of the research, after which they shall be disposed of with sufficient care to protect personal information. After that, dispose of them with care. Information on the computer should be completely deleted, and paper media (materials) should be shredded and disposed of.

